# Cognitive behaviour therapy plus aerobic exercise training to increase activity in patients with myotonic dystrophy type 1 (DM1) compared to usual care (OPTIMISTIC): study protocol for randomised controlled trial

**DOI:** 10.1186/s13063-015-0737-7

**Published:** 2015-05-23

**Keywords:** Myotonic dystrophy type 1, DM1, Cognitive behavioural therapy, Aerobic exercise training, Rare diseases

## Abstract

**Background:**

Myotonic dystrophy type 1 (DM1) is a rare, inherited chronic progressive disease as well as an autosomal dominant multi-systemic disorder. It is probably one of the most common adult forms of muscular dystrophy, with a prevalence of approximately 10 per 100,000 people affected. With 733 million people in Europe, we estimate that 75,000 people in Europe are affected with DM1.

**Methods/Design:**

OPTIMISTIC is a multi-centre, randomised trial designed to compare an intervention comprising cognitive behavioural therapy (CBT) plus graded exercise therapy against standard care. Participants will be recruited from myotonic dystrophy clinics and neuromuscular centres in France, Germany, the Netherlands and the United Kingdom. A sample size of 208 individuals is needed. To allow for some potential loss to follow-up, a total of 296 male and female patients aged 18 years and older with genetically proven classical or adult DM1 and suffering from severe fatigue (only DM1 patients with a Checklist Individual Strength (CIS) subscale fatigue severity score ≥35 are likely to benefit from the intervention), able to walk independently and able to complete the trial interventions will be included.

The primary outcome of the study is the score on the DM1-Activ scale, which is a measure of activity and participation for patients with DM1. Secondary outcomes include the 6-minute walk test, objective physical activity measured with an accelerometer, quality of life and cognitive measures. The trial will also collect data on potential effect modifiers of the short- and long-term clinical response, including pain, muscular impairment and cognitive-behavioural variables. In addition, OPTIMISTIC will identify genetic factors that predict outcome and potential biomarkers as surrogate outcome measures that best explain the observed clinical variation.

**Discussion:**

OPTIMISTIC will not only provide effectiveness data on an intervention that could fill a treatment-gap for DM1 patients but will also improve our understanding of the relevant determinants of the prognosis of DM1.

**Trial registration:**

Registration number: Cinicaltrials.gov NCT02118779; registered 11 April 2014.

## Background

Myotonic dystrophy type 1 (DM1) is a rare, inherited, progressive disease as well as an autosomal dominant multi-systemic disorder. It is one of the most common adult forms of muscular dystrophy, with a prevalence of approximately 10 per 100,000 people affected [1, 2]. With 733 million people in Europe, we estimate that 75,000 are DM1 patients [3]. Typical symptoms of the disease include progressive muscle weakness and wasting from distal to proximal, ptosis; weakness of facial, jaw and anterior neck muscles; myotonia; daytime sleepiness; fatigue and cataracts. Other symptoms of adult DM1 include cardiac conduction defects, as well as endocrine, gastrointestinal and cognitive dysfunction. DM1 is one of the most variable human diseases, has complex, multi-systemic and progressively worsening clinical manifestations and leads to severe physical impairment, restricted social participation and premature death [4, 5].

There is no pharmaceutical treatment for causal or symptomatic relief of DM1 core symptoms, with the exception of Modafinil for excessive daytime sleepiness and mexiletine for myotonia. Thus, the aim of treatment is to relieve impairments, reduce limitations and optimise participation. Physical activity has been acknowledged as an important factor for health in general. For patients with a slowly progressive neuromuscular disease, such as DM1, there is accumulating evidence for prescribing low-to-moderate-intensity strength and aerobic exercise training, and an active lifestyle [6]. Nevertheless, recent reviews conclude that existing studies are limited in number and quality, and that there is a need for disease-specific, randomised, controlled trials investigating the effect on quality of life [6–8].

### Rationale for the study

It was demonstrated recently by OPTIMISTIC Partner 1 (see *The OPTIMISTIC Consortium* for list of partners) that severe fatigue, defined as a score equal to or higher than 35 on the subscale fatigue of the Checklist Individual Strength (CIS-fatigue), was reported by around 70 % of patients with DM1 [9]. These severely fatigued patients had more problems with physical and social functioning as well as with their mental and general health than similar patients without severe fatigue. They also had more problems with concentration and planning. As such, experienced fatigue should be clearly distinguished from muscle weakness, which is probably the most common and characteristic symptom of DM1 and also of a lack of initiative (apathy) that is known to occur often in DM1.

In a longitudinal study, we built a model of perpetuating factors for fatigue in patients with DM1 (Fig. 1). It appeared that lack of physical activity, sleep disturbances and pain all contributed to experienced fatigue. In addition, loss of muscle strength and pain contributed to fatigue through a lower level of physical activity. Ultimately, experienced fatigue and physical activity both contributed to the level of societal participation [10]. A lack of initiative (motivation in the model of Fig. 1) further increased fatigue but also had a direct negative effect on societal participation. Thus, theoretically, in order to improve societal participation one should compensate for a reduced initiative, optimise physical activity and alleviate experienced fatigue. To alleviate fatigue one should address the fatigue maintaining factors identified by the model, for example, experience of pain or sleep disorders.

**Fig. 1 Fig1:**
[figure not shown]
Determinants of health status in DM1. Exercise therapy is intended to improve physical activity whereas cognitive behavioural therapy is intended to stimulate an active life-style by addressing perpetuating factors of fatigue such as lack of physical activity, motivation, pain and sleep disturbances and also by teaching patients to compensate for a lack of initiative (motivation)

The main rationale for the combination of CBT and physical exercise training is based on our DM1-specific model [10] (Fig. 1). The DM1-specific model shows that physical activity, experienced fatigue and lack of initiative are the main determinants of DM1 health status. OPTIMISTIC is the first model-based clinical trial in DM1. It evaluates the effect, and the maintenance of effects, of CBT combined with exercise training on the reduction of chronic fatigue in patients with DM1.

Importantly, the intervention will also involve caregivers where they are willing to take part. The disabilities associated with DM1 put considerable strain on caregivers and can also lead to a negative interaction with the patient. The intervention will aim to support caregivers by installing realistic expectations about what can be expected from the patient, teach caregivers how to help patients to stay as self-reliant as possible and also reduce caregivers strain by taking time for themselves. If a DM1 patient has no caregiver or significant other, or no caregiver or significant other willing to take part in the study, the patient will not be excluded from the study. All patients will be asked if the study team can approach him or her to inform them of further research. This contact does not constitute consent.

### Objectives

#### Primary objective

The primary objectives of this study are to evaluate the effect of a tailored behavioural change intervention comprising CBT and graded exercise on participation (as measured by the DM1-Activ scale) for severely fatigued patients with myotonic dystrophy type 1 compared to standard care.

#### Secondary objectives

The secondary objectives of this study are as follows:the creation and introduction of evidence based clinical guidelines on exercise and cognitive behavioural therapy combined with graded exercise in DM1,the identification of individual (serum, deoxyribonucleic acid (DNA)) or composite biomarker profiles as surrogate outcome measures and moderating or mediating factors of the efficacy and safety of the clinical response, andthe creation of a clinical trial infrastructure for European DM1 trials, including the collection of natural history data from a large cohort of DM1 patients.

## Methods/Design

### Study description

OPTIMISTIC is a two-arm, multi-centre, randomised controlled trial designed to compare cognitive behavioural therapy, plus graded exercise against standard patient management regimes. It is expected that the trial and outcome work will lead to new clinical guidelines for DM1 management. The intervention comprises cognitive behavioural therapy (CBT) and graded exercise therapy, both of which aim to achieve a more active lifestyle.

The effectiveness of this intervention, together with any adverse events associated with it, will be compared to standard patient management. Outcome measures will be measured at baseline; 0 to 5 week period depending if separate screening and baseline visits are required, 5 months (± 1 month, 10 months (± 1 month, the end of the intervention period) and at 6 months (± 1 month) post intervention (that is, 16 months from baseline, Fig. 2).

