### Study population

#### Number of participants

Participants will be recruited from myotonic dystrophy clinics and neuromuscular centres in the UK, the Netherlands, Germany and France. A total of 296 (male and female) patients will be recruited (see *Inclusion criteria* and *Exclusion criteria*). The figure of 296 allows for drop-outs; 208 are needed to complete the study with regard to our primary outcome (the DM1-Activ scale). This sample size for the primary outcome means that the study is also powered for one of the secondary outcomes, the 6-minute walk test. See *Sample Size Calculation* for more details with regard to participant numbers.

Participants will be randomised to receive a 10-month tailored behavioural change intervention (n = 148) or standard care (n = 148). The flow of participants through the trial is shown in Fig. 3.

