### Withdrawal procedures

#### Withdrawal from randomised therapy

Any clinician involved in the usual care of patients may withdraw patients from randomised intervention therapy using his/her clinical judgement. This might occur due to the occurrence of an adverse event and the onset of symptoms that limit tolerability. Participants withdrawn from randomised intervention therapy will remain in the study and will be included in the primary intention-to-treat analysis unless they request that their data are removed. If withdrawal is due to an adverse event it will be logged as such on the Adverse Event Log. All reasons for withdrawal will be noted in the participant’s Case Report Form and medical case notes. The participant and carer will be invited to attend the withdrawal visit. The measurements and activities scheduled at Visit 5 will be performed in the priority set out in the schedule table Appendix incorporating the participants and carers preferences. If a participant is randomised into the study with an immediate family member and either withdraw the other will be able to continue in the study.

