
The intervention will be delivered by therapists who have received extensive training before the trial starts and will use a standardised treatment manual developed by the OPTIMISTIC team. Prior to participating in the graded activity module, the treating clinician will make a judgment as to the degree of physical activity the participant is safely capable of doing, which will be communicated to the therapists. The therapists will remain in contact with the treating clinician throughout the trial to discuss any changes. The therapists and/or the research nurse can request that the treating physician/Investigator to review the patient at any time if any of the research team, the patient or the carer have any concerns. If required, the patients’ GP will be informed.

Participants will receive a workbook containing relevant information and assignments. If deemed appropriate a patient may be given a gym membership to assist with their set goals. If participants give their permission, CBT sessions will be audio recorded and transcribed. Transcriptions will be anonymised. Audio recordings will be stored securely at local sites and destroyed as described under *Study record retention*.

Between sessions participants will do ‘home-work’ assignments that are discussed in the subsequent session. If caregivers are involved in the intervention, they will be asked to support the patient in carrying out these assignments. Treatment integrity will be determined by two experienced cognitive behavioural therapists, who will independently rate a random selection of audio-taped sessions. During the intervention period phone calls to participants will be made at least once a week between sessions to remind them to complete any homework and to ensure attendance at sessions. Where it is felt necessary and resources allow participants will be visited in their homes to increase adherence and provide support where needed.

The intervention runs for 10 months but is front-loaded, meaning the first 4 months can be considered the ‘active’ phase with the remaining 6 months in the ‘booster’ phase. In this period of 10 months a patient will receive 10 to 14 sessions; at least 5 of them are face to face sessions. For the other sessions the therapist can decide, dependent on the traveling distance and the mobility of the patient, to use telephone contact or video conferencing as an alternative.

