#### Comparison

Standard care is the usual care at the participating site. This will vary by site and according to individual patient symptoms but the minimum is generally an annual visit plus ECG/EKG. Other care may include appropriate history taking, physical examination, ECG/EKG (or more in depth cardiac investigations), pulmonary and gastrointestinal investigations, and rehabilitation measures.

All control group participants will visit their trial site at baseline and months 5, 10 and 16 months post intervention (that is, 16 months from baseline) for the measurements as detailed in Appendix.

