### Study and safety assessments

A number of factors affecting the trial population suggest that we would expect to observe a larger than normal incidence of episodes of adverse events (AEs) such as fatigue and ill health due to co-morbidities of the study population. All known disease progression and co-morbidities will be noted but not reported.

Due to the large amount of co-morbid diseases that we expect to be present in the population, we will record, but not report, Serious Adverse Events (SAE) in the following categories:Any new cardiovascular event,Any new treatment of myotonic dystrophy type 1,Any hospitalisation due to falls or fractures,Any hospitalisation due to exacerbation of an existing medical condition, andAny elective or planned investigation or treatment.

All unexpected SAEs (that is, an SAE that is not listed above) will be recorded and reported to the sponsor. An example of an unexpected SAE would be premature death of a participant that was not due to an existing condition.

Safety assessments will be recorded at every visit.

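### The promised between-arm comparison of adverse events is open to ascertainment bias during the 10-month intervention, because events learned through therapy contact can reach the common log in one arm only

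*Protocol article*

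**What the plan says.** The Study description commits the trial to a comparison of harms: "The effectiveness of this intervention, together with any adverse events associated with it, will be compared to standard patient management".

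The scheduled collection does not differ by arm. Study and safety assessments says "Safety assessments will be recorded at every visit", and the measurement schedule in the Appendix has a single adverse-event row covering baseline and months 5, 10 and 16. For controls, the Comparison section says "All control group participants will visit their trial site at baseline and months 5, 10 and 16 months".

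The treated arm has further contact. Under Behavioural change intervention:

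- "In this period of 10 months a patient will receive 10 to 14 sessions", at least five of them face to face.
- "During the intervention period phone calls to participants will be made at least once a week between sessions"; the stated purpose is homework reminders and attendance.
- Home visits are possible, and therapists stay in touch with the treating clinician throughout.
- "The therapists and/or the research nurse can request that the treating physician/Investigator to review the patient at any time".

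Under Withdrawal from randomised therapy, which concerns participants taken off the intervention: "If withdrawal is due to an adverse event it will be logged as such on the Adverse Event Log".

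**The concern.** A between-arm comparison of adverse events is fair only if an event has about the same chance of being found in either arm. Here the scheduled enquiry is equal, but the unscheduled opportunities to hear of an event are not. A fall, an overuse injury or a spell of worse fatigue in a treated participant may come up in that week's call or session, prompt a clinical review and be logged. The same event in a control must be volunteered at a visit months later, or be found in the notes.

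This population makes the difference matter more. The article expects an unusually high rate of adverse events from co-morbidity, and describes patients with poor concentration, poor planning and low initiative, who may recall or volunteer events less reliably.

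Two errors are possible. More logged events in the treated arm could be read as harm when they reflect closer contact, or a true excess from exercise could be dismissed as an effect of closer contact. Without a record of how each event came to light, the two cannot be told apart afterwards.

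**Working it through.** The article gives no adverse-event rate, capture rate or safety power, so there is no stated figure to reproduce. The check counts contacts and then illustrates the mechanism.

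**1. Contacts in months 0 to 10**

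- Length: 10 × 365.25 / 12 / 7 = 43.5 weeks.
- Treated arm, lower count (one contact a week, either a call or a session): about 43.
- Treated arm, higher count (a call every week plus 14 sessions): about 43 + 14 = 57.
- Both arms: two follow-up visits in this period (months 5 and 10), plus a reminder call the day before each scheduled visit.

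**2. Longest interval between common visits while therapy is running**

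The visits at months 5 and 10 each have a window of ±1 month. The nominal gap is 10 − 5 = 5 months. The longest runs from month 4 to month 11, so 11 − 4 = 7 months.

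**3. Routes by which an event can reach the log, months 0 to 10**

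| Route | Treated | Control |
|---|---|---|
| Scheduled visit enquiry | yes | yes |
| Medical notes, usual care | yes | yes |
| Therapy session | yes | no |
| Weekly call | yes | no |
| Review requested under the intervention section | yes | not described |
| Event logged as reason for ending therapy | yes | in practice no |

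**4. What unequal capture would do (assumed figures, not from the documents)**

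Let the true proportion of participants with an event be p in both arms, with capture shares c_T (treated) and c_C (control). The apparent risk ratio is (p × c_T) / (p × c_C) = c_T / c_C. Take c_T = 1, p = 0.40 and 148 per arm, with a two-sided 5% test of two proportions:

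| Control capture | Observed risks | Apparent risk ratio | Chance of a significant difference |
|---|---|---|---|
| 100% | 0.40 v 0.40 | 1.00 | 5% |
| 90% | 0.40 v 0.36 | 1.11 | about 10% |
| 80% | 0.40 v 0.32 | 1.25 | about 30% |
| 70% | 0.40 v 0.28 | 1.43 | about 59% |

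At 80% control capture, the chance runs from about 14% (p = 0.20) to about 55% (p = 0.60). If the comparison counts only events found through routes open to both arms, with equal capture, c_T / c_C = 1 and this source of bias largely goes.

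**The case against.** The case on the other side has real force.

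- **Collection as scheduled is symmetric.** There is one adverse-event row and one rule for safety assessment. This stands, and it limits the point to events learned outside the common visits.
- **Nothing says that calls or sessions feed the safety data.** The calls are for homework and attendance. This also stands: the article is silent, so these are incidental routes. But therapists are in contact with the treating clinician and reviews can be requested, so events can reach the log this way, and no rule shown deals with them.
- **Controls are not invisible.** They receive usual care, and Data collection names the medical notes as possible source data for later conditions and hospital admissions, without restriction by arm. Admissions are therefore the events least affected.
- **More contact is inherent in comparing a therapy with usual care**, and may itself prime recall at the common visits. True, and the fix below does not remove that part.
- **Detail of this kind may sit in the full protocol, the CRF or the analysis plan.** It may, and then one confirming sentence settles the matter. The point rests on two things the article does state: the comparison and the unequal contact.

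A reader might go further and infer that the comparison is biased by a known amount, that the treated arm has its own adverse-event log, that a control's event is known only if recalled, or that the safety question cannot be answered. The documents support none of these. There is one common log; the withdrawal rule adds a trigger for an entry, not a separate system; notes and usual care also bring control events to light; and capture rates are not given. Nor does the interval before the month 16 visit count as a control-only gap, since therapy ends at month 10 and neither arm has scheduled sessions for most of it.

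**Conclusion.** The point holds as a risk in the design of the comparison. If all logged events are tabulated by arm, that table is open to ascertainment bias in months 0 to 10. With equal true harm, the expected direction is towards more recorded events in the treated arm. The contact imbalance is large (about 43 to 57 treated-arm contacts beside two common follow-up visits), but contact is not capture, and the size of any bias cannot be estimated from the documents. The risk ratios of 1.11 to 1.43 rest wholly on assumed capture of 70% to 90% in controls and complete capture in treated participants. They show only that a modest difference in capture could matter with 148 per arm. The primary efficacy analysis is not affected.

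**What to change.** 1. Add a source field to the Adverse Event Log: common scheduled visit or medical notes, versus therapy session, call, unscheduled review or withdrawal from therapy.
2. At Visits 3, 4 and 5, put the same adverse-event question to both arms, covering the whole interval since the previous visit. Check the medical notes for hospital admissions in both arms in the same way.
3. Base the main between-arm comparison on events elicited or confirmed through these common routes. An event first heard of in a session still counts if the visit enquiry or the notes check also finds it.
4. Beside it, show the all-events table by arm, marking events known only from therapy contact. Every event is still recorded and acted on, and no known harm is left out of the report.

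The cost is one log field, one standard question at visits that already take place, a notes check and one extra safety table. The drawback is that the two tables may differ, and the report will have to explain why.
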